**Methods/Design:**

Healthy old people (n = 54) between the age of 65 to 80 years will participate in this trial. The testing protocol comprises tests for the assessment of static / dynamic steady-state balance (i.e., Sharpened Romberg Test, instrumented gait analysis), proactive balance (i.e., Functional Reach Test; Timed Up and Go Test), reactive balance (i.e., perturbation test during bipedal stance; Push and Release Test), strength (i.e., hand grip strength test; Chair Stand Test), and power (i.e., Stair Climb Power Test; countermovement jump). Further, body composition will be analysed using a bioelectrical impedance analysis system. In addition, questionnaires for the assessment of psychosocial (i.e., World Health Organisation Quality of Life Assessment-Bref), cognitive (i.e., Mini Mental State Examination), and fall risk determinants (i.e., Fall Efficacy Scale – International) will be included in the study protocol. Participants will be randomized into two intervention groups or the control / waiting group. After baseline measures, participants in the intervention groups will conduct a 12-week balance and strength / power exercise intervention 3 times per week, with each training session lasting 30 min. (actual training time). One intervention group will complete an extensive supervised training program, while the other intervention group will complete a short version ('3 times 3’) that is home-based and controlled by weekly phone calls. Post-tests will be conducted right after the intervention period. Additionally, detraining effects will be measured 12 weeks after program cessation. The control group / waiting group will not participate in any specific intervention during the experimental period, but will receive the extensive supervised program after the experimental period.

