### Balance and strength / power assessment

The primary outcome measures will be balance and strength / power at baseline (pre-test), after the intervention (post-test) and 12 weeks after the intervention (follow-up). In general, balance assessment will be performed before strength / power assessment to reduce interfering effects of muscle fatigue [64].

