### Statistics and sample size

An a priori power analysis was conducted to detect the sample size that is necessary to find statistically significant exercise effects [93] based on a study assessing the effects of balance training on postural control in older adults [94]. Considering a dropout rate of 10%, 18 participants per arm will be required to achieve 90% power (type II error of 0.10) with a type I error of 5%. Data will be analysed using a 2- and 3-way repeated measures analysis of variance (ANOVA) consisting of groups (INT1, INT2, CON) and time (pre-test, post-test, follow-up). Bonferroni post-hoc test will be used for statically significant (p < .05) group and time differences. Associations between clinical and biomechanical tests will be reported by their correlation coefficient (r value), level of significance (p value) and the amount of variance explained (r^2^ value). Values of r = 0.10 indicate a small, r = 0.30 a medium and r = 0.50 a large-size correlation [i.e., effect size] [95].

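### Bonferroni after a significant ANOVA is valid but needlessly conservative for the three arm contrasts of one change score; a closed or step-down test holds the same 5% with more power

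*Protocol article*

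**What the plan says.** All of the plan's text on this point is in the protocol article, Statistics and sample size. The model is given as "Data will be analysed using a 2- and 3-way repeated measures analysis of variance (ANOVA"), with factors "groups (INT1, INT2, CON) and time (pre-test, post-test, follow-up"). The next sentence sets the multiplicity rule: a "Bonferroni post-hoc test will be used for statically significant (p < .05) group and time differences". The natural reading is an omnibus test at 5% and, if it is significant, pairwise tests with a Bonferroni correction. The article does not spell out the family over which Bonferroni is taken; a fuller plan may do so.

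The same section sets 18 participants per arm for 90% power at a 5% type I error with 10% dropout. The calculation is described as "based on a study assessing the effects of balance training on postural control in older adults", without an effect size, standard deviation or tested contrast.

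**The concern.** With three arms there are three pairwise hypotheses, and if any two are true the third is true as well. A valid omnibus test at 5% therefore already does the work that dividing by three is meant to do, so for that family the same error is controlled twice.

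What is at stake is the comparison of programmes. The Discussion looks to the two intervention arms for an indication of the minimum exercise dose, and asks whether the short home version works. Those questions are INT2 vs CON and INT1 vs INT2, the contrasts in which a weaker effect is most easily missed with about 16 completers per arm.

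**Working it through.** **Inputs.** From the article: three arms, 18 per arm, 10% dropout, 5% type I error, 90% power. Assumed: two-sided tests, normal change scores, equal variances, pooled error, and effect sizes d in units of the SD of the change.

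**The plan's own figure.** Only the dropout step can be reproduced: 16 / 0.9 = 17.8, rounded up to 18, and 3 x 18 = 54. The 18 itself cannot be re-derived without an effect size. As a reference effect, take the d that gives one unadjusted two-arm comparison 90% power at n = 16. The normal formula gives d = (1.960 + 1.282) x sqrt(2/16) = 1.15; the t distribution gives 1.185, used below as 1.18. At 5%/3 = 1.67%, the same two-sample test at d = 1.185 has 78.7% power, or about 80% with the error pooled over three arms.

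**Why 5% is held without Bonferroni.** Two cases are enough.
- All three arms equal: the closed test makes an error only if the omnibus test is significant, which has probability 5%. Shaffer's step-down makes an error only if the smallest p-value is below 5%/3, which has probability at most 3 x 5%/3 = 5%.
- Exactly one pair equal: only one hypothesis can be falsely rejected, and it is tested at no more than 5%.

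**Simulation, one three-arm family, n = 16 per arm.**

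| Assumed truth | Quantity | Omnibus + Bonferroni | Omnibus + unadjusted (closed) | Shaffer, no omnibus |
|---|---|---|---|---|
| all arms equal | family-wise error | 4.2% | 5.0% | at most 5% |
| two arms equal, third far away | family-wise error | 1.6% | 5.0% | at most 5% |
| both programmes d = 1.18 | each vs CON | 80% | 88% | 86% |
| both programmes d = 1.18 | both found | 69% | 84% | 82% |
| INT1 1.18, INT2 0.59 | INT2 vs CON | 22% | 37% | 36% |

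With both programmes at d = 0.8, the closed test gives 52% against 42% per programme, and 43% against 26% for finding both.

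**Where the argument stops.**
- *Group-by-time interaction.* It has (3-1) x (3-1) = 4 df and up to nine pairwise contrasts. With correlation 0.5 between visits and only INT1 differing, unadjusted pairs after a significant interaction give a family-wise error of 18-24%. Division by 3 gives 6.6-9.3% and division by 9 gives 2.4-3.3%.
- *Two change scores.* Separate 5% families for the post-test and follow-up changes hold about 5% each, but about 9% over both. The interaction test with pairs at 5%/3 gives 3.7% when all arms are equal and 3.1-5.9% when only INT1 differs.
- *Three visits.* Under an assumed non-spherical covariance (correlations 0.9, 0.3, 0.3) and an uncorrected F test, omnibus plus unadjusted pairs gives 6.4%, and omnibus plus Bonferroni 2.5%.

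**The case against.** The strongest objection is that this is not a one-way comparison of three means. In a randomised trial measured before, after and at follow-up, the treatment effect lies in the group-by-time interaction, where the three-means result fails and a correction is needed. A reader might infer that Bonferroni costs power for nothing throughout the plan and should be struck out. The documents do not support that: the design has three arms and three visits, and unadjusted pairs after the interaction would raise the error well above 5%. This part of the objection stands, and the point is limited accordingly.

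It also stands that the visit comparison needs a valid within-subject F test, that separate families for the two changes loosen control per measure, and that the power figures describe a single change score rather than the full repeated measures ANOVA. Nor does the rule much affect the chance of finding at least one true difference: with one arm differing by d = 1.19, it is 91% under the plan's rule and 93% under the closed test.

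What remains is narrower. Among the three arm contrasts of one change, Bonferroni is dominated: Shaffer's step-down rejects everything Bonferroni rejects, sometimes more, at the same 5%. This also holds if the interaction test is kept as the first step. In the three-by-three layout with correlation 0.5, Shaffer after the interaction test kept the error at no more than 5.1% per contrast. Power for INT2 vs CON at d = 0.59 rose from 21% to 34%.

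**Conclusion.** The concern holds as a matter of efficiency for one family: the three arm contrasts of a single change score. There the planned rule spends only 1.6-4.2% of the 5% allowed. It costs about 6-8 points of power per programme when both have d = 1.18, 13-15 points for finding both, and about 14-15 points for a programme at d = 0.59.

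These losses rest on assumed effect sizes, 16 completers per arm, normal change scores and equal variances. The article states no effect size, so they illustrate the size of the loss and do not predict it.

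Two further inferences should be resisted. The planned rule is not a failure of type I error control; it errs on the safe side for three means. Nor does this show that the stated 90% power is wrong: the contrast and effect behind it are not given, so it cannot be checked against the post-hoc rule.

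**What to change.** 1. **Pre-to-post change, three arm contrasts.** Replace Bonferroni by Shaffer's step-down: test the smallest p-value at 5%/3 and, if it is significant, each of the other two at 5%. Alternatively, test the change with one 2-df omnibus test at 5% and, if it is significant, each pair at an unadjusted 5%. If the 4-df interaction stays as the first step, use the step-down and not unadjusted pairs.
2. **Follow-up (detraining) change.** Either declare it a separate family and say that control is per contrast, about 9% over both, or keep 5% per measure. For the latter, use Holm over all six contrasts, or open the follow-up family only after all three pre-to-post contrasts are rejected. Opening it after any one rejection is not enough, because a remaining true pre-to-post null and the follow-up family could each spend 5%.
3. **Three visits.** Use the omnibus-then-unadjusted rule only with a sphericity-corrected F test; otherwise use Holm.

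The cost is a few sentences of analysis text, with no new data and no change in sample size. There are two downsides. The step-down tests have no matching simultaneous confidence intervals, so Bonferroni intervals should be reported beside them. Holm over six starts at 5%/6, stricter than 5%/3, so choosing strict control per measure gives back some of the gain.

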The proposed trial presented in this article will investigate the effects of a fall prevention exercise program developed by an expert panel on intrinsic fall risk factors (i.e., balance, strength / power), body composition, cognitive function, psychosocial well-being, and falls-self efficacy. The applied research tools will allow diagnosis of sarcopenia according to the EWGSOP guidelines. Thus, we will be able to evaluate prevalence of sarcopenia in our participants, and conduct sensitivity and specificity analysis for the strength / power assessments including their cut-offs. To facilitate transfer into clinical practice, simple clinical tests for each instrumented test will be provided to alleviate fall risk assessment and exercise prescription adjustment. In addition to an easy implementation into practice, this will allow cross-validation of the applied research instruments (clinical vs. instrumented). Further, this work may help to promote the protocol of the expert panel and the rationale behind the practice guide to people with English as their native language. We hypothesize that our training program will positively influence balance, strength / power, body composition as well as cognition, psychosocial well-being, and falls-self efficacy in older community-dwelling people.

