Dynamic steady-state balance will be tested while walking on an instrumented 10-m walkway using a two-dimensional OptoGait^©^-System (Bolzano, Italy). Participants will walk with their own footwear at self-selected speeds, initiating and terminating each walk a minimum of 2 m before and after the 10-m walkway to allow sufficient distance to accelerate to and decelerate from a steady-state of ambulation across the walkway. The rectangular OptoGait^©^-System is an opto-electrical measurement system consisting of transmitting and receiving bars for obtaining a two-dimensional measurement area. Each bar is 1 m in length and contains 100 LEDs that transmit continuously to each other. With a continuous connection between the two bars, any break in the connection can be measured and timed. The walking pattern will be monitored at 1,000 Hz, enabling spatial and temporal gait data to be collected. The OptoGait^©^-System demonstrated high discriminant and concurrent validity with a validated electronic walkway (GAITRite^©^-System) for the assessment of spatio-temporal gait parameters in orthopedic patients and healthy controls [67]. Hausdorff et al. [68] reported that spatio-temporal parameters of gait are important mobility markers in community-dwelling older adults. Thus, means and standard deviations (SD) of stride time, stride length, stride velocity, and stride width will be computed. In addition, coefficients of variation (CV) for stride time, stride length, stride velocity, and stride width will be calculated according to the following formula: [CV = (SD / mean) × 100] [69]. Of note, the CV is a sensitive and clinically relevant marker for increased fall risk [70]. Further, it has been reported that gait velocity below 70 cm/s is associated with an increased risk of falling in old community-dwelling adults [71]. Thus, using a stopwatch to the nearest 0.01 s, gait velocity will be assessed as a marker of fall risk. Granacher et al. [72] recently reported that intraclass correlation coefficient (ICC) values for the above reported gait parameters were above 0.75. To resemble real life situations, static and dynamic steady-state balance will be tested under single (standing / walking) and dual task (standing / walking while counting backwards aloud) conditions. The cognitive interference task will comprise an arithmetic task, in which the participants recite out loud serial subtractions by three starting from a randomly selected number between 300 and 900 given by the experimenter [73].

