The current trial will add valuable information to the knowledge of dose–response-relations for exercise in older adults. Particularly the use of two different intervention arms (extensive supervised group exercise program vs. short home-based exercise program) will give some indication of the minimal amount of exercise needed to stimulate physical performance adaptations. If the short version of the program (3 times per week for 30 min.) will prove to be effective, this may lower the barrier for sedentary older adults to take up exercising. If intrinsic fall risk factors can be positively influenced by our proposed intervention regime, future trials will need to investigate any possible effect on fall rate in older adults. Additionally, in this trial, each clinical test will be compared to a gold-standard instrumented test. This cross-validation may facilitate the implementation of easy-to-administer balance and strength / power assessments into practice. Regular simple balance and strength / power assessments are important for training prescription and performance regarding exercise variation and progression. Furthermore, measuring gait velocity, grip strength and muscle mass will allow diagnosis of sarcopenia according to EWGSOP criteria, and may add knowledge to sensitivity and specificity of strength / power test to this important geriatric syndrome.

In summary, this trial will provide insight into the effect of fall prevention exercise applicable for a broad population and setting, both in community and sporting groups and at home. Practitioners, exercise therapists, and instructors will be provided with a feasible, validated exercise routine whose effect on intrinsic fall risk factors is scientifically evaluated. Furthermore, older adults who participate in the present program represent possible multipliers for a broader acceptance of important exercise and health-enhancing measures. Finally, the results of the current trial may help to further develop theories and models explaining balance and resistance training effects in general and particularly in older adults.

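### The clinical-versus-instrumented comparison is called a cross-validation against a gold standard, but the analysis named for it (r, its p value and r-squared) can show association only

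*Protocol article*

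**What the plan says.** **Purpose.** The last paragraph of the Background promises that "simple clinical tests for each instrumented test will be provided to alleviate fall risk assessment and exercise prescription adjustment" and that "this will allow cross-validation of the applied research instruments (clinical vs. instrumented"). The Discussion repeats this: "in this trial, each clinical test will be compared to a gold-standard instrumented test. This cross-validation may facilitate the implementation". It then ties such tests to training: "Regular simple balance and strength / power assessments are important for training prescription and performance regarding exercise variation and progression". The clinical tests are thus meant to classify people and to guide training in the same person over time.

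**Analysis.** Statistics and sample size names r and its p value ("Associations between clinical and biomechanical tests will be reported by their correlation coefficient (r value), level of significance (p value") and adds "the amount of variance explained (r^2^ value"). The yardstick follows: "Values of r = 0.10 indicate a small, r = 0.30 a medium and r = 0.50 a large-size correlation". The article does not say which visit is used, or whether levels or changes are correlated. It names no measure of agreement and no criterion for calling a test validated.

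**A pair in the same unit.** Under Balance assessment and gait analysis, OptoGait yields stride velocity on the 10-m walkway, and "using a stopwatch to the nearest 0.01 s, gait velocity will be assessed as a marker of fall risk". A fall-risk cut-off of 70 cm/s is cited there. The Background cites 80 cm/s as a sarcopenia criterion.

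**The concern.** Validating a clinical test against a gold standard raises two questions. Does it give the right value where both methods measure the same thing? Does it move when the instrument moves? A correlation answers neither directly.

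- A constant or proportional error leaves r almost unchanged, yet the clinical value is read against fixed cut-offs.
- Stable differences between people (age, build, fitness) make two tests correlate at one visit even if their training responses are unrelated.
- The r-squared value and the size labels do not repair this, because they are functions of the same r.

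At stake is a stated secondary product of the trial: advice to practitioners on which simple tests can stand in for instruments.

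**Working it through.** The article gives no figure for this analysis, so there is none to reproduce. Inputs from the documents: N = 54; 10% dropout, leaving about 48 (54 × 0.9 = 48.6); alpha 5%, taken as two-sided; ICCs of 0.69 and 0.40 for platform oscillation and 0.84 for the Push and Release Test. Other inputs are marked as assumed.

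**1. What p < .05 requires.** Critical r = t / √(n − 2 + t²).
- n = 54: t = 2.007, r = 2.007 / √(52 + 4.03) = 0.268, r² = 7.2%.
- n = 48: t = 2.013, r = 2.013 / √(46 + 4.05) = 0.285, r² = 8.1%.

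**2. Precision of a large r.** Fisher z for 0.50 is 0.549. The half-width at n = 54 is 1.96 / √51 = 0.274. Transforming 0.275 and 0.824 back gives 0.27 to 0.68, so the interval starts below the medium label. At n = 48 it is 0.25 to 0.69.

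**3. Systematic error.** Assumed: true speed mean 110 and SD 20 cm/s; stopwatch reading = (1 + b) × true speed + random error of SD 4 cm/s. Then r = 20(1 + b) / √(400(1 + b)² + 16). The mean difference is 110b, and its SD is √((20b)² + 16).

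| Over-reading b | r | Mean difference (limits of agreement), cm/s | Missed among those ≤ 80 cm/s | Missed among those ≤ 70 cm/s |
|---|---|---|---|---|
| 0% | 0.98 | 0 (−7.8 to 7.8) | 13% | 15% |
| 5% | 0.98 | 5.5 (−2.6 to 13.6) | 31% | 33% |
| 10% | 0.98 | 11.0 (2.2 to 19.8) | 50% | 51% |

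The correlation does not move; the mean difference shows the error at once. The counts are small: under these assumptions 6.7% of 54, about 3.6 people, are at or below 80 cm/s, and 2.3%, about 1.2 people, at or below 70 cm/s.

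**4. Following change.** Assumed: 48 completers, reliability 0.85, individual training responses of SD 0.5 that are unrelated between the two tests. Simulated share of trials with p < .05 for a between-person r of 0.3, 0.4, 0.5 and 0.6:
- pre-test correlation: 42%, 67%, 87%, 97%;
- post-test correlation: 31%, 51%, 70%, 85%;
- correlation of pre-to-post changes: about 5%.

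A single-visit r therefore says little about responsiveness.

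**5. Can change correlations decide the matter instead?** Take perfect tracking, with trait SD 1 and response variance 0.25. Error variance per test is (1 − ICC) / ICC, and it enters a change twice.
- Both ICCs 0.85: 0.25 / (0.25 + 2 × 0.176) = 0.41.
- ICCs 0.69 and 0.84: 0.25 / √((0.25 + 2 × 0.449)(0.25 + 2 × 0.190)) = 0.29.
- ICCs 0.40 and 0.84: 0.25 / √((0.25 + 2 × 1.5)(0.25 + 2 × 0.190)) = 0.17.

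A perfectly tracking test would thus show a modest change correlation. Pooling arms adds the opposite fault. Suppose individual responses are unrelated but two of three arms gain g on both tests. The shared variance is g² × (2/3)(1/3). For g = 0.8 it is 0.142, and r = 0.142 / (0.603 + 0.142) = 0.19. For g = 1.0 it is 0.222, and r = 0.222 / (0.603 + 0.222) = 0.27. In simulation these reach p < .05 in roughly a quarter and a half of trials. Removing arm means brings this back to about 5%.

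**The case against.** A reader might infer that any pair with p < .05 will be declared validated. The article does not say so. It undertakes to report r, p and r-squared, and it gives size labels, so an r of 0.27 would appear as 7% shared variance and below medium. A clinical test *can* look validated; nothing says that it *will*.

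A reader might also infer that r hides every kind of mis-measurement. It hides systematic error only. Random error lowers r: the cited ICCs cap it at √(0.69 × 0.84) = 0.76 and √(0.40 × 0.84) = 0.58 for the Push and Release Test against the two oscillation measures.

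Nor does the article rule out an analysis of change. The visit is simply not stated, and a full analysis plan may settle it.

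Three further points stand in the plan's favour.
- Most pairs measure different quantities (stair-climb power and jump, Push and Release rating and platform oscillation, standing time and centre-of-pressure displacement). Agreement statistics do not apply there, and correlation is a normal measure of convergent validity.
- The group-by-time ANOVA can show at group level whether a clinical test responds, though not whether it follows the instrument in individuals.
- Sensitivity and specificity at cut-offs are planned for the strength and power tests, but with respect to sarcopenia, not the instrumented partner.

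These points narrow the concern. They do not close the gap between the claim and the statistics named for it, both of which the article states.

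**Conclusion.** The point holds as a mismatch between claim and method. The named statistics support a statement of association. They do not support cross-validation against a gold standard for classifying people or steering training. Firm figures: r of 0.27 suffices for p < .05 at 54 participants, and an observed 0.50 is compatible with 0.27 to 0.68. The illustrations of bias and of unrelated training responses rest on assumed speeds, timing error, reliability and response SD. No stopwatch bias of 5% or 10% is given in the documents. The misclassification percentages concern about one to four people, and treating OptoGait and stopwatch velocity as a pair is a reading of the gait section. The remedy is cheap and worth making, but this is a secondary aim: the comparison of the three arms on balance and strength / power is not touched.

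**What to change.** Under Statistics and sample size:

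1. For stopwatch gait velocity and OptoGait velocity, report the mean difference, the limits of agreement and classification agreement at the two cited cut-offs, noting that few participants may fall below them. State whether both values come from the same walk, since otherwise the difference includes walk-to-walk variation.
2. For all other pairs, report r with its 95% confidence interval, state the visit used, and describe the result as association (convergent validity), not validation.
3. Report pre-to-post change correlations adjusted for arm, with 95% confidence intervals, as supportive evidence only. They should not be a pass criterion, because measurement error attenuates them strongly and, without adjustment for arm, they reflect group mean gains.

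Limit the cross-validation wording in the Background and Discussion to what these results can carry.

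The cost is a few sentences and slightly more analysis of measurements already planned in all arms before and after the intervention and at follow-up. No visits, tests or participants are added. The price is a more modest claim.
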